**Methods:**

A cluster randomized controlled trial including 70 classes with older adolescents (aged 16 years or older) in the Netherlands will be conducted to test the effectiveness of the InCharge program. After schools are recruited, randomization occurs at the class level. The trial consists of the following two conditions: an experimental condition and a control condition. Participants in the experimental condition will be given the InCharge intervention, consisting of four lessons of 50 minutes, with each lesson containing three assignments of approximately 15 minutes. While participants in the experimental condition will receive InCharge, participants in the control condition will receive regular academic school courses. Surveys are administered 1 week before the intervention (baseline), 1 week after the intervention (posttest), and 12 weeks after the intervention (follow-up). Variables of interest include, but are not limited to, self-regulation; predictors of snack intake, physical activity, and alcohol use; and interpersonal communication regarding these health behaviors. In addition to surveys, observations will be conducted during the first and fourth lessons, teachers will be interviewed, and focus groups will be held with a selection of students from the intervention condition.

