## Methods

### Study Design

The InCharge effectiveness study is a cluster RCT including the following two conditions: an experimental condition (the InCharge program) and a control condition (no intervention) (Figure 1). Participants are older adolescents (aged 16 years or older) in schools for intermediate vocational education, schools for higher general secondary education, and schools for preuniversity education. After initial recruitment and enrollment of schools in the trial, randomization takes place at the class level. In each school, measurements in both experimental and control classes are scheduled 1 week before the four lessons of the InCharge program are implemented in the experimental classes (baseline), and 1 week (posttest) and 3 months (follow-up) after the experimental classes have completed the InCharge program. In addition, the first and fourth lessons of the program are observed by two independent coders in order to obtain information on how the program is delivered, interviews are conducted with teachers about their experiences with the program, and focus groups are conducted with small groups of students about their experiences with the program (both interviews and focus groups are conducted 1 week after the posttest assessment). After all data have been collected within a school, control classes will also receive the intervention.

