In the second lesson, the concept of self-regulation is introduced (for students, self-regulation is called willpower). First, students watch and discuss a video of the marshmallow experiment to understand the role of self-regulation [30]. In this experiment, young children are offered a choice between one marshmallow provided immediately or two marshmallows after waiting for a short period of time. The second assignment focuses on previous experiences with willpower. Students are asked to discuss their own experiences with succeeded challenges, together with the applied strategies that helped them succeed. Finally, all students prepare a challenge to complete during the next week to train their self-regulation abilities. First, they set a realistic goal for themselves related to a chosen health behavior, after which they create a specific plan to achieve this goal. This plan includes the identification of difficult situations and the selection of coping strategies to address these situations accordingly. The actual challenge is completed as a homework assignment. With the help of a specially designed smartphone app (the 7-day challenge), students monitor their progress.

In the third lesson, first, the results of the 7-day challenge are discussed. During the second assignment, students reflect on their original plan to complete the challenge and discuss how these plans could further be improved. The third assignment addresses peer pressure, as peers have been shown to strongly influence the health behaviors of adolescents [31,32]. In order to grasp the influence of peer pressure, students watch and discuss a video of an experiment with a test subject sitting in a room with confederates. As the room fills up with smoke, all confederates remain calm as if nothing happens. As a result, the test subject also remains seated, which could actually be life threatening in case of a real fire.

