The final lesson elaborates on alcohol use. At first, students watch a video of partying adolescents who are consuming large amounts of alcohol. The video shows a group of friends who are having fun at first, but the situation ends with a conflict and an injury as a result of excessive alcohol use. Thereafter, students discuss the role of peer pressure in excessive drinking. Second, in order to make them aware of current social norms, students discuss the social acceptability of binge drinking by means of an interactive web-based quiz. Finally, the students identify situations in their own life, where it is important to be careful with alcohol, and come up with strategies to do so. A more thorough description of the assignments can be found in Multimedia Appendix 1.

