### Outcomes

#### Questionnaire Data

The InCharge program aims to stimulate a healthier lifestyle in general among older adolescents by increasing self-regulation skills. In terms of outcome measures, the study focuses on the following three outcome behaviors: alcohol use, snack intake, and lack of physical activity. A pilot study of the program has shown that these behaviors are most prevalent among older adolescents. The main outcomes that are measured for alcohol use, snack intake, and physical activity are the actual behaviors and predictors of the behaviors. Snack behavior and physical activity are operationalized as the number of times adolescents consume snacks and are physically active in an ordinary week as well as in the past 7 days [33]. Alcohol use is operationalized as the number of times adolescents drink alcohol and engage in binge drinking in the past 4 weeks (ie, frequency), as well as the number of drinks adolescents usually consume on one occasion (ie, quantity). Moreover, the predictors of these behaviors are operationalized according to the TPB as attitudes, subjective norms, perceived behavioral control, and behavioral intention [20]. As an additional predictor, negative outcome expectancies are defined as the anticipated negative result of a certain behavior [34]. We operationalized negative outcome expectancies as the probability that exercising less than once a week or daily snacking will lead to weight increase, a poor condition, and health-related problems. For alcohol use, negative outcome expectancies are operationalized as the probability that drinking more than five glasses of alcohol on one occasion will lead to sickness, loss of control, blackouts, regret, and violence (including sexual violence). Finally, parental rules for the three behaviors are assessed.

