### Statistical Analysis

The background variables of the students (eg, gender, age, and educational level) will be checked to assess whether these variables are successfully randomized across the experimental and control conditions. Unsuccessfully randomized variables will be included as covariates in further analyses to control for potential confounding. Our data have a multilevel structure because participants are nested within classes, and these classes are nested within schools. Therefore, participants in one class or school are more similar than participants in other classes or schools. To account for this potential dependency in the data, we will correct standard errors and parameter estimates for clustering.

In order to determine the effectiveness of the health intervention, an intention-to-treat procedure and completers-only framework will be used to analyze the data. An intention-to-treat analysis of the data implies that participants will be analyzed under the condition that they are initially assigned, whereas completers-only framework analyzes only participants who are present at all time points. Using multilevel analyses, the three behavioral outcomes (snack intake, physical activity, and alcohol use) will be compared between participants in the experimental condition and those in the control condition at posttest and follow-up to determine the effects of the program. In the experimental condition only, multilevel analyses will be conducted to investigate the influence of treatment integrity on the predictors of the three health behaviors at posttest and follow-up. For missing data in multilevel models, maximum likelihood estimation will be used. As self-regulation is an important concept in InCharge, we will test whether the potential effects of InCharge on the health behaviors are explained by self-control. Additionally, relations between interpersonal communication with teachers, friends, classmates, and parents (ie, frequency and valence) and health-related outcomes, such as a mediating role between the conditions and outcomes, will be tested. As the program is delivered by teachers, we will also test in the experimental condition whether teacher communication relates to the evaluations of the health intervention and the three behavioral outcomes, using structural equation modeling. For structural equation models, expectation maximization will be used to impute the data.

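### At posttest, three of the four weeks counted for drinking and binge-drinking frequency precede programme completion, so the posttest comparison of these two items is likely diluted as a measure of the post-programme effect

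*Protocol article*

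**What the plan says.** All references are to the protocol article.

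- **Recall period.** Questionnaire Data: "Alcohol use is operationalized as the number of times adolescents drink alcohol and engage in binge drinking in the past 4 weeks". A third alcohol measure has no fixed window: "the number of drinks adolescents usually consume on one occasion (ie, quantity". Snacking and physical activity are asked "in an ordinary week as well as in the past 7 days".
- **Timing.** Study Design places the measurements "1 week (posttest) and 3 months (follow-up) after the experimental classes have completed the InCharge program". The abstract gives the follow-up as 12 weeks.
- **Order of content.** InCharge Program: "The final lesson elaborates on alcohol use". This is lesson 4 of 4.
- **Use of the posttest.** Statistical Analysis compares the three behaviours, alcohol use among them, between conditions "at posttest and follow-up to determine the effects of the program".
- **What is claimed.** Aim and Hypotheses expects less binge drinking once students have finished the programme. Strengths and Limitations says the design can assess both short-term and medium-term effects. The limitations listed there do not mention the recall period.

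**The concern.** Each of these choices is reasonable alone; the difficulty is how they combine. A 4-week count taken 1 week after the last lesson includes only one week of post-programme behaviour. For snacking and activity the protocol has a 7-day item that fits the 1-week gap exactly, but drinking and binge frequency have no such item.

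Binge drinking is named in the hypothesis and in the programme's main objective. A posttest null on it could be reported as no short-term effect when most of the counted drinking took place before the alcohol lesson. A posttest null followed by a difference at 12 weeks could be misread as delayed onset. The Conclusion says the programme will be improved on the basis of the findings, so such a misreading could have practical consequences.

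**Working it through.** **Inputs from the protocol article**

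- Recall of 4 weeks for drinking and binge frequency (Questionnaire Data).
- Posttest 1 week after completion, follow-up at 12 weeks (Study Design; abstract).
- d = 0.2, two-sided alpha 0.05, power 0.80, ICC 0.025, 16 students per class, 35 classes and 560 students per condition (Sample Size Calculation).

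**Assumptions, not in the documents**

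- Weekly lessons. Only the gap between lessons 2 and 3 is indicated: "all students prepare a challenge to complete during the next week to train their self-regulation abilities".
- Drinking spread evenly across weeks, with the standard deviation of the 4-week count unchanged, so that d shrinks in proportion to the affected share of the window.

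**Step 1: reproduce the plan's sample size.** n per arm = 2 × (1.960 + 0.842)² / 0.2² = 392.4, rounded up to 393, as stated. Design effect = 1 + (16 − 1) × 0.025 = 1.375. Then 393 × 1.375 = 540.4 students, or 33.8 classes, rounded up to 34 classes (544 students). The stated 560 is 2.9% higher, and one extra class per arm gives it exactly. The plan's figure is accepted.

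**Step 2: window overlap.** Share before completion = (recall − weeks since completion) / recall.

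- Posttest, 4-week items: (4 − 1)/4 = 75%. This holds whatever the lesson spacing.
- Follow-up at 12 weeks: the window covers weeks 8 to 12 after completion, so 0%.
- Posttest, 7-day items: 0%.

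**Step 3: effect on the posttest contrast.** SE of d = √(2 × 1.375 / 560) = 0.0701. Power ≈ Φ(d/0.0701 − 1.96).

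| Onset of the effect (weekly lessons) | Share retained | Expected d | Power |
|---|---|---|---|
| Only after lesson 4 | 1/4 | 0.05 | 11% |
| In full from lesson 3 | 2/4 | 0.10 | 30% |
| Equal increment after each lesson: (0.25 + 0.50 + 0.75 + 1)/4 | 0.625 | 0.125 | 43% |
| In full from lesson 2 | 3/4 | 0.15 | 57% |
| Undiluted | 1 | 0.20 | 81% |

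With a t reference on 68 degrees of freedom (70 classes − 2), the values for d = 0.05, 0.10, 0.15 and 0.20 are 10.8%, 29.0%, 56.0% and 80.3%, which is the same picture.

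**Step 4: sensitivity to lesson spacing.** The first row does not depend on spacing. The others do: with wider gaps, fewer of the three pre-completion weeks would precede lesson 2 or 3, and dilution would be smaller. With closer gaps, part of the window would precede lesson 1 altogether.

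**The case against.** The strongest reply is that the analysis tests the programme, not lesson 4. The stated mechanism is self-regulation, which is built up over all the lessons. Alcohol is among the temptations discussed in lesson 1, lesson 2 sets a challenge on a health behaviour the student chooses, and lesson 3 covers peer pressure. With weekly lessons the posttest window opens at about lesson 1, so all of it follows first exposure. This stands: coming before completion is not the same as coming before exposure, and the size of the dilution is unknown. It does not remove the mismatch, because dilution is absent only if the full effect is present from the start of the window, which is implausible when alcohol is the topic of the last lesson.

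It is also fair to say that the posttest holds other alcohol evidence. Table 1 lists intentions, attitudes, social norms, outcome expectancies and self-efficacy at posttest, with no 4-week recall stated. These, and usual drinks per occasion, lie outside this point.

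A reader might infer more than the documents support:

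- *That the posttest could hardly have detected an effect.* The 11% is the worst case, with no effect at all from lessons 1 to 3. Other assumed onsets give 30% to 57%.
- *That the ordinary-week snack and activity items share the fault.* Those items have no stated look-back, so no overlap can be computed.
- *That the posttest is given the same weight as the follow-up.* Statistical Analysis names both without ranking them, and Strengths and Limitations distinguishes short-term from medium-term effects.
- *That the sample size is wrong.* It is set for a generic d of 0.2, not for posttest alcohol frequency.

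**Conclusion.** The point holds for two items, drinking frequency and binge-drinking frequency, at the posttest only. That 75% of their window precedes completion and the alcohol lesson follows directly from the stated recall and timing. The likely direction is towards no difference, and the 12-week comparison is free of the overlap.

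The magnitude is a scenario range and not a derived figure: expected d of about 0.05 to 0.15 in place of 0.2, with power of about 11% to 57% against about 80%. It rests on weekly lessons, even drinking across weeks, and the protocol's generic effect size. The undiluted figure describes the follow-up only if the effect has not faded by then.

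The two posttest comparisons are not invalid as descriptions of drinking over the 4 weeks before the posttest. They are poorly matched to the post-completion hypothesis and to the claim of assessing short-term effects, and the article does not say so.

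**What to change.** - **Questionnaire Data and Statistical Analysis:** state that the post-programme effect on drinking frequency and binge-drinking frequency is judged at the 12-week follow-up, where the recall window lies wholly after completion.
- **Reporting of the posttest:** keep both items, label them as covering mainly the programme period, and state that a null result there is not evidence against a short-term effect.
- **Strengths and Limitations:** qualify the short-term claim for these two items.

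The change should be dated and made before outcome data are examined by arm, because moving the time point of judgement later would invite suspicion of selection. The article does not state that data collection is complete; its Results section describes it as ongoing.

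The cost is wording, with no new data needed. The price is that the short-term claim for these two items is given up, and an effect that fades before the follow-up window could be missed.

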#### Observational Data

Observations are conducted during delivery of the first and fourth lessons of InCharge to provide information on the classroom processes and how the program is delivered (Multimedia Appendices 2 and 3). The main outcomes of the observations are treatment integrity (ie, adherence to the protocol), interpersonal communication during the intervention, classroom interactional processes, teaching style, and student participation. First, treatment integrity or adherence is operationalized as the extent to which the delivered intervention resembles the intended intervention [39]. Additionally, we assess whether the teacher appears to support the intervention. Second, interpersonal communication is operationalized as the number of times a student or teacher talks about the three outcome behaviors during plenary discussions. We also assess whether a student or teacher initiates these discussions about the three outcome behaviors, whether comments during the plenary discussions are based on own experiences, and whether a student or teacher gives suggestions to increase self-efficacy regarding the three behaviors. Third, classroom interactional processes consist of three dimensions, namely emotional support (eg, positive climate), classroom organization (eg, behavior management), and instructional support (eg, quality of feedback [40]). Fourth, teaching style consists of the two components warmth and control [41]. Finally, we code several characteristics referring to student behavior, such as student participations, disruptive behaviors, and general class atmosphere.

#### Qualitative Data

The topic list of the focus groups with students includes interpersonal communication about temptations, evaluations of the InCharge program, and evaluations of the teacher. For interpersonal communication, we investigate the motivation to discuss temptations with the teacher, friends, classmates, and parents, and reasons why students did not discuss temptations with these conversational partners. The content as well as the valence of the conversations about temptations is investigated for interpersonal communication both within class and outside class. For the evaluation of the program, we aim to understand what parts of the intervention students find helpful or not, whether students actively complete in-class and homework assignments, and whether students think the intervention helps them to deal with temptations in the future. Lastly, we ask students about whether their teacher clearly explains the assignments during the intervention, who should ideally be given these interventions, and their perceptions of their teacher’s support for the intervention.

The topic list of interviews with teachers includes interpersonal communication, teacher perception of students, and evaluation of InCharge. For interpersonal communication, we assess the content and valence of conversations with students about the InCharge program, both during the intervention and outside class, as well as conversations that teachers have overheard among students. For teacher perception of students, we investigate how teachers perceive students’ participation and enjoyment. Finally, we discuss the health intervention with the teacher in order to find improvements for the program.

### Statistical Analysis

The background variables of the students (eg, gender, age, and educational level) will be checked to assess whether these variables are successfully randomized across the experimental and control conditions. Unsuccessfully randomized variables will be included as covariates in further analyses to control for potential confounding. Our data have a multilevel structure because participants are nested within classes, and these classes are nested within schools. Therefore, participants in one class or school are more similar than participants in other classes or schools. To account for this potential dependency in the data, we will correct standard errors and parameter estimates for clustering.

In order to determine the effectiveness of the health intervention, an intention-to-treat procedure and completers-only framework will be used to analyze the data. An intention-to-treat analysis of the data implies that participants will be analyzed under the condition that they are initially assigned, whereas completers-only framework analyzes only participants who are present at all time points. Using multilevel analyses, the three behavioral outcomes (snack intake, physical activity, and alcohol use) will be compared between participants in the experimental condition and those in the control condition at posttest and follow-up to determine the effects of the program. In the experimental condition only, multilevel analyses will be conducted to investigate the influence of treatment integrity on the predictors of the three health behaviors at posttest and follow-up. For missing data in multilevel models, maximum likelihood estimation will be used. As self-regulation is an important concept in InCharge, we will test whether the potential effects of InCharge on the health behaviors are explained by self-control. Additionally, relations between interpersonal communication with teachers, friends, classmates, and parents (ie, frequency and valence) and health-related outcomes, such as a mediating role between the conditions and outcomes, will be tested. As the program is delivered by teachers, we will also test in the experimental condition whether teacher communication relates to the evaluations of the health intervention and the three behavioral outcomes, using structural equation modeling. For structural equation models, expectation maximization will be used to impute the data.

For the qualitative data, interviews with teachers and focus groups with students will be analyzed on the strengths and weaknesses of the program in order to adapt the program. Furthermore, qualitative data will be used to determine the content of interpersonal communication with regard to the InCharge program and various temptations.

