### Participants

#### Recruitment

The Municipal Health Services and prevention departments of regional institutions for the treatment and care of addiction help to implement the InCharge program in schools. From these Municipal Health Services and regional institutions, 47 prevention practitioners are trained by the Trimbos Institute to instruct teachers on how to deliver the program and are asked to provide us with a list of schools in their region interested in participating in the InCharge study. The research team contacts these schools to explain the objective and design of the study. First, schools receive an invitation and an information brochure via email, and thereafter, schools are contacted by phone to discuss participation in the study. Schools are allowed to select the number of classes participating in the study, with a minimum of two classes because randomization occurs within schools. To create comparable research conditions, schools are instructed that a minimum number of two classes should be from the same educational level of the field of study. Classes are eligible for inclusion in the study if they contain older adolescents and the level of education is intermediate vocational education, higher general secondary education, or preuniversity education. Students are recruited by class participation. In collaboration with the schools, students’ parents are informed about the study objectives and receive passive informed consent forms. Written active informed consent is obtained from all participating students.

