#### Randomization

We randomize the participants at the class level, and classes within schools are matched on the school level in order to obtain more comparable research conditions. Classes are randomly allocated to the experimental or control condition by means of repeated coin tossing. For each selection of matched classes within schools, classes are assigned to the experimental condition if the coin toss shows heads and to the control condition if the coin toss shows tails. The coin toss procedure is continued until all matched classes are assigned to a research condition, such that as many matched classes as possible are assigned to the experimental and control conditions. Randomization is carried out centrally, with two researchers present to monitor the procedure.

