**Alcohol, snacking, and physical activity**				
	Actual behavior	X	X	X
	Intentions	X	X	X
	Attitudes	X	X	X
	Social norms	X	X	X
	Negative outcome expectancies	X	X	X
	Self-efficacy	X	X	X
	Perceived parental rules	X	—^b^	—

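### Covariates are chosen by observed baseline imbalance with no stated criterion, so the effect model depends on chance and achievable precision is given away

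*Protocol article*

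**What the plan says.** All of this is in the protocol article.

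- **Statistical Analysis, the check.** "The background variables of the students (eg, gender, age, and educational level) will be checked" to see whether randomisation succeeded.
- **Statistical Analysis, the consequence.** "Unsuccessfully randomized variables will be included as covariates in further analyses to control for potential confounding". No test, threshold or level of analysis (student or class) is given for the check.
- **Statistical Analysis, the effect model.** "Using multilevel analyses, the three behavioral outcomes (snack intake, physical activity, and alcohol use) will be compared" between conditions at posttest and follow-up. The section notes that "participants are nested within classes, and these classes are nested within schools" and adds that "we will correct standard errors and parameter estimates for clustering".
- **Randomization.** Allocation is by class, and "classes within schools are matched on the school level in order to obtain more comparable research conditions".
- **Recruitment.** Schools are told that "a minimum number of two classes should be from the same educational level of the field of study".
- **Table 1.** The three behaviours themselves are measured at baseline, posttest and follow-up.

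**The concern.** Classes are allocated by coin toss, so a baseline difference between conditions is the product of chance. A check cannot show that a variable was randomised without success. Nor does the size of a difference say whether adjusting for the variable is useful: a strong predictor that happens to look balanced can stay out, and an irrelevant variable that happens to differ comes in.

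Three things are at stake.

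- **The model is not fixed in advance.** Without a criterion, the covariate set for three behaviours at two time points is settled after the data are seen.
- **Precision.** Adjusting for a predictive covariate reduces residual variance whether or not it is balanced. The rule takes that gain only in the few trials where the check fires.
- **Educational level.** Schools are asked for classes of the same level so that the conditions are comparable. The variable will therefore tend to look balanced, and the rule will tend to leave it out.

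**Working it through.** **Inputs from the Sample Size Calculation section:** d = 0.2, two-sided alpha 0.05, power 0.80, ICC 0.025, 16 students per class, 35 classes (560 students) per condition.

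**Assumptions, not in the article:** the check is a test at p<0.05, and the covariate-outcome correlation r runs from 0.1 to 0.7.

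**1. The plan's own figure.** The unclustered size reproduces as 393 per condition. The design effect is 1 + (16 − 1) × 0.025 = 1.375, so 393 × 1.375 = 540.4 students, or 33.8 classes. With a t reference on 2(k − 1) degrees of freedom, 34 classes give 79.2% power and 35 classes give 80.3%. The planned 35 classes (560 students) is reproduced. No covariate gain is built into it.

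**2. The two-stage rule.** Let Zx be the standardised baseline difference and Zy the unadjusted test statistic, with correlation r. The adjusted statistic is (Zy − r·Zx)/√(1 − r²), which is independent of Zx. The rule uses the adjusted statistic if |Zx| > 1.96 and Zy otherwise. Power is evaluated where the unadjusted test has 80%, that is, at noncentrality 1.960 + 0.842 = 2.802. Under fixed adjustment the noncentrality becomes 2.802/√(1 − r²); at r = 0.5 this is 2.802/0.866 = 3.235, giving 89.9%.

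| r | Type I error, rule | Power, rule | Power, fixed adjustment | Forgone (points) |
|---|---|---|---|---|
| 0.1 | 5.0% | 80.0% | 80.4% | 0.4 |
| 0.2 | 4.9% | 80.2% | 81.6% | 1.4 |
| 0.3 | 4.8% | 80.4% | 83.6% | 3.2 |
| 0.5 | 4.3% | 81.1% | 89.9% | 8.8 |
| 0.7 | 3.6% | 82.0% | 97.5% | 15.5 |

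Fixed adjustment holds 5% throughout. The rule is conservative for a simple reason. When the check fires, the unadjusted test would reject too often (9.8%, 18.5% and 33.1% at r = 0.3, 0.5 and 0.7), and the rule replaces it. When the check does not fire, the unadjusted test is kept and rejects too rarely (about 4.8%, 4.3% and 3.5%).

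**3. Simulation at the trial's own size.** Settings: 35 + 35 classes of 16, d = 0.2, outcome and covariate ICC 0.025, with 6,000 null and 3,000 alternative runs. The Monte Carlo standard errors are about √(0.05 × 0.95/6000) = 0.3 points for type I error and √(0.8 × 0.2/3000) = 0.7 points for power. Ranges cover a check at student level and one at class level.

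| r | Type I error, rule | Power, rule | Power, fixed adjustment |
|---|---|---|---|
| 0.3 | 4.4–5.2% | 81% | 83–84% |
| 0.5 | 4.5% | 81–83% | 89% |
| 0.7 | 3.2–3.8% | 82–84% | 98% |

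This agrees with step 2.

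**4. How often chance fires the check.** With a correctly calibrated test at 0.05 and three independent variables, the chance of at least one flag is 1 − 0.95³ = 14.3%. If the check ignored classes and allocation were unmatched, the flag rate per variable would be 2(1 − Φ(1.96/√(1 + 15 × ICC))). That is 9.5% at covariate ICC 0.025 and 21.5% at 0.10; the simulation gave 9–10% and 22%.

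**The case against.** The strongest reply is that the harm is small for the variables named. Gender, age and educational level may well have r of 0.3 or less with these behaviours. In that range the rule costs about 0 to 3 points of power and leaves type I error near nominal. The larger losses need a covariate as predictive as a baseline value of the outcome, which the sentence does not clearly cover. This stands, and it limits the severity.

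A reader might also infer more than the article supports:

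- **That the rule raises the false-positive risk.** It does not; the deviation is conservative.
- **That the rule takes the trial below its planned power.** It does not. The sample size assumes no covariate, and power under the rule is at or slightly above that of the unadjusted test. The loss is a forgone gain. Figures below 80% arise only if the outcome ICC is allowed to exceed the protocol's 0.025, and then the unadjusted test is below 80% as well.
- **That the matching factors are dropped.** School is named as a level in the analysis. What is left to the check is educational level.
- **That the check is miscalibrated.** The flag rates of 9.5% and 21.5% hold only for a check that ignores classes, with unmatched allocation. The article does not say how the check is done, and allocation is matched.
- **That baseline behaviour is excluded from the model.** The article does not say so. A fuller plan may include it, and its absence from a condensed article is no error.

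None of this defends the rule itself. It is stated, not merely left open, and it makes chance imbalance a condition for entering the model.

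**Conclusion.** The point holds in limited form and should be fixed. Choosing covariates by an undefined imbalance check leaves the effect model open until the data are seen, makes the test mildly conservative (about 4.8% at r = 0.3, 3.6% at r = 0.7) and forgoes power against fixed adjustment: about 0 to 3 points for r up to 0.3, and 9 to 16 points for r of 0.5 to 0.7. The sizes rest on an assumed p<0.05 check and assumed correlations. The direction does not depend on the exact correlation, provided the covariate predicts the outcome. The planned 80% power and the control of false positives are not threatened.

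**What to change.** Delete the sentence that lets imbalance decide the covariates. In its place, name covariates that enter every effect model whatever the observed balance:

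- the baseline value of the outcome being analysed (Table 1 shows it is already collected: "Actual behavior X X X");
- educational level;
- sex and age.

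Keep school, or the matched set, in the model. If matched sets are fitted as fixed effects and are formed within educational level, they already carry that variable. Present the baseline table as description only, with no test that decides the model.

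The cost is one replaced sentence and no new data. The covariates use a few degrees of freedom. Matched sets as fixed effects use more: an unmatched class-level comparison has 70 − 2 = 68, and if every set were a pair (an assumption), 35 set effects plus the treatment effect would leave 70 − 36 = 34.
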